**Figure 4. F0004:**
[figure not shown]
Locations of acupuncture points used in sham electroacupuncture group. Yellow dots: acupoints used for locating non-acupoints; blue dots: non-acupoints. NA: Non-acupoint, GB14: Yangbai, SJ6: Waiguan, CV15: Jiuwei, CV12: Zhongwan, CV9: Shuifen, CV5: Shimen, LU6: Kongzui, GB34: Yanglingquan, SP6: Sanyinjiao.

**Table 2. t0002:** Locations of non-acupuncture points used in sham electroacupuncture group.

Non-acupoints	Location
NA1-2	3 cun lateral to the GB14 (On the forehead, 1 cun directly above the midpoint of the eyebrow) horizontally.
NA3-4	1 cun lateral to the CV15 (Below the xiphoid process, 7 cun above the umbilicus, locate the point in supine position with the arms uplifted) horizontally.
NA5-6	1 cun lateral to the CV12 (On the midline of the abdomen, 4 cun above the umbilicus) horizontally.
NA7-8	1 cun lateral to the CV9 (On the midline of the abdomen, 1 cun above the umbilicus) horizontally.
NA9-10	1 cun lateral to the CV5 (On the midline of the abdomen, 2 cun below the umbilicus) horizontally.
NA11-12	On the side of the abdomen, 2 cun above the anterior superior iliac spine.
NA13-14	1 cun lateral to the SJ6 (3 cun above SJ 4, between the radius and the ulna, on the radial side of muscle extensor digitorum) horizontally.
NA15-16	3 cun lateral to the LU6 (The point is on the palm aspect of the forearm, on the line joining Lu 9 and Lu 5, 7 cun above the transverse crease of the wrist) horizontally.
NA17-18	3 cun inferior to the GB34 (In the depression anterior and inferior to the head of the fibula) vertically.
NA19-20	1 cun inferior to the SP6 (3 cun directly above the tip of the medial malleolus, on the posterior border of the medial aspect of the tibia) vertically.

NA: Non-acupoint, GB14: Yangbai, CV15: Jiuwei, CV12: Zhongwan, CV9: Shuifen, CV5: Shimen, SJ6: Waiguan, LU6: Kongzui, GB34: Yanglingquan, SP6: Sanyinjiao.

#### Permitted and prohibited concomitant treatments

2.5.3.

All participants will be permitted to treat insomnia with zopiclone (7.5 mg/T, Guangdong Cr.shunfeng Pharmaceutical Co., Ltd., Guangdong, China, taken orally, 3.75 mg each time) as their first choice for acute medication during the trial. The name, dosage, and timing of usage will be recorded in the sleep diary.

### Outcomes

2.6.

#### Primary outcome measurement

2.6.1.

The primary is the response rate, which reflects the proportion of participants whose average Insomnia Severity Index (ISI) scores decrease by at least 7 units [30,31] at Week 4 compared with baseline. The ISI is a 7-item self-administrated instrument to evaluate the nature, severity, and impact of insomnia during daytime and nighttime. A 5-point Likert scale is used to score each item, consisting of a total score ranging from 0 to 28: where 0–7 = No clinically significant insomnia, 8–14 = Subthreshold insomnia, 15–21 = Clinical insomnia (moderate severity), 22–28 = Clinical insomnia (severe) [31,32]. The minimal clinically important difference (MCID) of ISI is 7 units [30,31].

#### Secondary outcome measurement

2.6.2.

Sleep diary: Participants will be required to complete a daily sleep diary during the whole trial, the variables in the daily sleep diary include sleep onset latency, wake after sleep onset, early morning awakening, total wake time, total sleep time, and sleep efficiency [31].Insomnia Severity Index (ISI): ISI will also be used as one of the secondary outcomes, details of ISI are presented in primary outcome measurement section [31,32]. ISI will be applied at baseline, Week 4 and 8Pittsburgh Sleep Quality Index (PSQI): PSQI will be used to assess sleep quality and disturbances over the past month. PSQI is composed of 19 items including 4 open questions, and 15 Likert-type questions that score for each question ranging from 0 to 3. Individual item scores yield 7 components. The final score is acquired by adding the 7 component scores. Higher scores indicate more acute sleep disturbances, and a cut-off score of 5 suggests poor sleep quality [33]. PSQI will be applied at baseline, Week 4 and 8.Short Form Health Survey-12 (SF-12): SF-12 will be used to detect the quality of life. The SF-12 comprises both mental and physical components, with each part ranging between 0 and 100. Higher scores indicate a greater quality of life [34]. SF-12 will be applied at baseline, Week 4, and 8.Fatigue Severity Scale (FSS): FSS is a 9-item questionnaire and will be used to assess the severity of fatigue and how it affects certain activities. Each item is scored on a seven-point scale, the total score ranges from 9 to 63. Higher scores indicate more severe fatigue [35]. FSS will be applied at baseline, Week 4, and 8.(6) 24-Hour ambulatory blood pressure: 24-Hour ambulatory blood pressure monitoring will be applied as baseline, Week 4, and 8 to evaluate the night blood pressure, the results will be interpreted by a specific cardiovascular specialist.Blood sample: Blood samples will be collected at baseline, Week 4, and 8 to compare the levels of C-reactive protein (CRP) and D-Dimer.

#### Compliance assessment

2.6.3.

Participants who achieve scores above 80 will meet the criteria for good compliance by the end of Week 4.

$$\text{Compliance score}=\frac{\text{Acutual treatment sessions}}{\text{Required treatment sessions}}x100$$

E.g. a participant undergoes 6 treatment sessions, as 12 sessions are required in this study, based on the equation, the compliance score amounts to 50, denoting inadequate compliance.

#### Assessment of safety

2.6.4.

All adverse events will be assessed and recorded by proficient acupuncturists and outcome assessors after the end of each treatment and during the follow-up phase. Serious adverse events will be reported and handled according to relevant regulations. Common adverse events associated with acupuncture include persistent post-needling pain, dizziness, subcutaneous hematoma, infection, etc.

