### Blinding

2.4.

Throughout the trial, participants will be blinded, however, acupuncturists will not be blinded due to the nature of the intervention. Blinding of group assignments will also be enforced for data analysts and outcome assessors. The concealment of the allocation for all participants will be maintained until the statistical analysis has been completed.

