### Interventions

2.5.

The style of acupuncture is based on traditional Chinese medicine principle, and acupuncture prescription has been developed from literature review [27] as well as the clinical practice. Each participant will be ushered by a research assistant to hospital bed, which will be screened off separately one-by-one by opaque curtains. No companion will be allowed to stay with the participants during the treatment period. Acupuncturists should have a Chinese medicine practitioner license with at least 2 years of experience, and two acupuncturists will be given trial-specific training, such as the selection of acupuncture points and the usage of EA apparatus in different groups at the program launching session to realize their role and job in this study. Each participant will be performed EA or sham EA by the same acupuncturist throughout the trial. Also, two acupuncturists will not tell anyone else about the treatment allocation, and they will be asked to communicate with participants as less as possible to avoid inadvertent unblinding.

Sterile disposable acupuncture needles (length, 25–40 mm; diameter, 0.25–0.30 mm; Hwato Brand, Suzhou Medical Appliance Factory, Suzhou, China) and EA apparatus (HANS-200A acupoint nerve stimulator, Nanjing Jisheng Medical Co, Ltd) will be used in both groups. EA apparatus will be connected right after needles are inserted into all acupuncture points, and will be retained for 30 min. All participants will receive the same treatment according to their group. Both the treatment and sham groups will consist of 12-session intervention over 4 weeks (three sessions per week, ideally every other day). Intervention will be discontinued if the participants have any serious adverse events. All participants will be informed that the current of EA may not be perceived by human.

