There are several limitations in our study. First, the acupuncturists are not blinded. Therefore, acupuncturists may pay more attention to the participants in the treatment group, which may lead to the observed effects. Also, we use sham EA with false apparatus and superficial penetration on non-acupoints to isolate the specific effect of EA. Compared with placebo control, there is a possibility of having a therapeutic effect. However, we hypothesize that EA will have a better effect, so there is no need to set a placebo control group, and the sham control procedure has been successfully applied in previous study [29]. Moreover, our study is single-center, participants are from one hospital, which will cause limited representativeness of patients and poor extrapolation of our findings. However, single-center study has better internal authenticity compared with multi-center trials. Besides, the relatively small sample size may reduce the probability of rejecting a false null hypothesis, whereas, our study is a pilot study, a sample size of 30 for each group is recommended in previous studies. Finally, due to the treatment burden of patients with ESRD undergoing MHD, a fixed treatment schedule will not be set for everyone, we will suggest participants receiving treatment every other day, however, treatment schedule will be adjusted when overlapping MHD treatment.

In conclusion, we will conduct a single-center and two-arm RCT to investigate the efficacy and safety of EA for insomnia in ESRD undergoing MHD. We employ a strict methodology to minimize bias and form monitoring committees to guarantee the quality of the clinical trial, which provides evidence for further understanding and generalizing the clinical application of EA for insomnia in ESRD undergoing MHD.

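### Unblinded acupuncturists share in assessing adverse events that are then compared between arms, with no division of roles from the blinded assessors and no mention of this as a safety limitation

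*Protocol article*

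**What the plan says.** Section 2.6.4 (Assessment of safety) fixes who judges safety: "All adverse events will be assessed and recorded by proficient acupuncturists and outcome assessors". They do so after every session and through follow-up. The section does not say which group does what. The events it names as common are persistent post-needling pain, dizziness, subcutaneous hematoma and infection.

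Section 2.4 (Blinding) puts the two groups on opposite sides of the blind: "acupuncturists will not be blinded due to the nature of the intervention", and "Blinding of group assignments will also be enforced for data analysts and outcome assessors".

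Section 2.5 (Interventions) says that "two acupuncturists will be given trial-specific training" and that "Each participant will be performed EA or sham EA by the same acupuncturist throughout the trial". It also says of the acupuncturists that "they will be asked to communicate with participants as less as possible to avoid inadvertent unblinding".

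Section 2.8 (Statistical analysis) compares the adverse-event rate by a chi-squared test. The Introduction makes safety one of the two aims. The Discussion counts blinding of participants, outcome assessors and statisticians among the reasons why the evidence on efficacy and safety will be reliable. Its limitations paragraph concedes that "acupuncturists may pay more attention to the participants in the treatment group, which may lead to the observed effects", but does not extend this to the recording of adverse events.

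**The concern.** A between-arm comparison of adverse-event rates is fair only if events are found and recorded equally well in both arms. Here one of the two groups that assess them knows the allocation. Pain and dizziness come to light only if someone asks or the participant volunteers them, and whether a small hematoma or a sore point counts as an event is a matter of judgement. With the roles undivided, knowledge of the arm can affect both whether an event is recorded and how it is judged.

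A true difference is plausible. In the EA arm, needles at body and limb points go 20–30 mm deep with manipulation (section 2.5.1). In the sham arm they go 2–3 mm without it (section 2.5.2). Safety is therefore a comparison on which this pilot may be quoted, and the Discussion presents it as protected by blinding when it is only partly so.

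**Working it through.** **1. The article's own figures.** There is none to reproduce. Section 2.7 says that no formal sample size calculation was made, and no adverse-event rate is given anywhere. The finding rests on the text; the arithmetic only illustrates it.

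**2. The sections side by side.**
- Who assesses: acupuncturists and outcome assessors together (2.6.4).
- Who knows the arm: the acupuncturists do, the outcome assessors should not (2.4).
- Whether the assessing acupuncturists are the treating ones: 2.6.4 does not say so. But 2.5 has two trained acupuncturists and keeps each participant with the same one, and the assessment follows each session, so in practice they are.
- What is done with the record: a chi-squared test between arms (2.8).
- What is disclosed: unequal attention to participants, but nothing about safety recording (Discussion).

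**3. Illustration.** Inputs: 30 per arm (2.7). Assumed, because the article gives no values: true event proportions, recording proportions, and a two-sided alpha of 0.05, since 2.8 states none for adverse events. Recorded proportion = true proportion × proportion of events recorded. The rejection probability is the sum of the binomial probabilities of all 31 × 31 tables in which the uncorrected chi-squared exceeds its 5% critical value. For x and y events, chi-squared = (x − y)² × 60 / [(x + y)(60 − x − y)].

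*Equal true rates (any difference is false).* The figures are the same whichever arm is under-recorded.

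| True rate, both arms | Equal, full recording | 90% in one arm, 60% in the other | 100% in one arm, 50% in the other |
|---|---|---|---|
| 10% | 5.4% | 6.7% | 10.6% |
| 20% | 4.9% | 10.1% | 19.4% |
| 30% | 4.9% | 12.9% | 28.1% |
| 40% | 4.9% | 16.9% | 39.2% |

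*A true difference of 40% (EA) against 13.3% (sham).* Power with full recording is 67%.

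| Proportion recorded in the under-recorded arm | Power if EA is under-recorded | Power if sham is under-recorded |
|---|---|---|
| 90% | 54% | 72% |
| 80% | 41% | 77% |
| 70% | 28% | 82% |
| 60% | 18% | 86% |

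*One table.* 12/30 against 4/30 gives 64 × 60 / (16 × 44) = 5.45, p = 0.020. If 4 of the 12 EA events go unrecorded, 8/30 against 4/30 gives 16 × 60 / (12 × 48) = 1.67, p = 0.20.

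So unequal recording can hide a real difference, exaggerate it or invent one, depending on which arm is under-recorded.

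**4. Where the needles go.** From Table 1, the EA arm has eight scalp and hairline needles: GV20 (1), GV24 (1), EX-HN1 (4) and bilateral GB13 (2). From Table 2, the sham arm has two at forehead level (NA1-2) and none on the scalp. Both arms have needles in the abdomen, forearm or wrist, and lower leg.

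**The case against.** The person who places the needles sees immediate events first and cannot sensibly be kept from reporting them. That stands, and it is why the fix keeps factual reporting with the acupuncturist. Pairing them with blinded assessors is also a partial safeguard. Detailed grading and causality rules may sit in a fuller protocol or case report form, so their absence from an article is not the complaint. The complaint is what the article does fix: unblinded staff assess as well as record.

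Four stronger readings are tempting, and the article does not support them.

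- *Needle-site checks will unblind the outcome assessors.* No section describes assessors inspecting needle sites. Because scalp needles belong to the EA arm alone, the route is possible, but the assessor would have to see a scalp mark and know the point lists.
- *The efficacy results are compromised.* The ISI is self-administered (2.6.1). The other outcomes are a participant's diary, questionnaires, ambulatory blood pressure and blood tests (2.6.2). An assessor who learned the arm would have limited room to move these.
- *The instruction to say little to participants contradicts adverse-event assessment.* It limits conversation in order to protect the blind and does not bar asking about symptoms. The two duties pull against each other but can both be met.
- *EA events will be under-recorded.* The Discussion's remark about extra attention to the EA arm would, if anything, suggest fuller recording there. The article does not settle the direction.

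**Conclusion.** The point holds in a limited form. Acupuncturists who know the allocation, and in effect gave the treatment, jointly assess adverse events that are then tested between arms. Their role is not separated from that of the blinded assessors, and the limitations do not mention it for safety. The comparison is open to detection bias of unknown direction and size. The illustrative figures (false differences in 7% to 17% of trials at 90% against 60% recording, and up to 39% at 100% against 50%) rest wholly on assumed event and recording rates and an assumed alpha of 0.05. They show that the bias could matter with 30 per arm and do not measure it in this trial. That the assessing acupuncturists are the treating ones is an inference from section 2.5, though a strong one. This is a worthwhile, cheap improvement to the safety assessment and does not challenge the primary analysis.

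**What to change.** Amend section 2.6.4, using the staff it already names:

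1. The blinded outcome assessors put the same fixed symptom checklist to every participant after each session and during follow-up. This record is the source for the between-arm adverse-event rate in section 2.8.
2. The acupuncturists report immediate events as facts on a standard form (what was seen, where, what size) and do not grade severity or relatedness.
3. A blinded assessor grades severity and relatedness from a record that leaves out the group and the point names, but says whether the event is at a needle site or at the dialysis access. That distinction has to stay, because all participants have vascular access and receive heparin (section 2.5), so a hematoma or infection may have either origin.
4. If a needle site has to be looked at around Week 4 or Week 8, this is done once that visit's scales are complete. It is a precaution against the possible unblinding route through scalp needles.
5. The Discussion states that unblinded staff contribute to safety recording.

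The cost is protocol wording, a checklist and form, a few minutes per session, and loss of the acupuncturist's opinion on causality. No sample size or alpha changes. Section 2.2 expected enrolment to end by June 2024. If treatment is already over, items 1, 2 and 4 can no longer be applied, but masked grading may still be possible from existing records, and item 5 can be done in any case.

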### Sample size

2.7.

No previous study has been found to use the response rate to evaluate EA for insomnia in end-stage renal disease undergoing MHD. A formal sample size calculation is not necessary in our exploratory study. Thus, recruitment will take place for a participant sample size of 60, with 30 individuals per group, to obtain the practical aim of our study based on clinical experience [36].

### Statistical analysis

2.8.

A biostatistician, who is blinded to the data, is accountable for conducting statistical analyses employing SAS (SAS Institute located in Cary, NC, USA) and R software (version 4.2.1). Intention-to-treat (ITT) is our statistical strategy that includes all participants who have been randomized and received at least one intervention session. Demographic characteristics will be summarized for each group. Mean (standard deviation) or median (interquartile range) will be used to describe continuous variables depending on distribution’s normality. Percentage will be used to describe categorical variables. Regarding primary outcomes, a Chi-squared test will be applied to compare the response rate between treatment group and control group. For secondary outcomes, continuous variables including sleep diary, ISI, PSQI, SF-12, FSS, ambulatory blood pressure, and plasma levels of CRP and D-Dimer will be analyzed according to repeated measurement using a mixed-effects model. α will be set at 0.025 for the primary outcome, and it will be set at 0.05 for multiple comparisons of the secondary outcomes. Besides, the 95% confidence interval (95% CI) will be used to assess effect size of primary and secondary outcomes. A Chi-squared test will be applied for the compliance scores and adverse events rate. Last observation carried forward method will be used for the dropout analysis. Sensitivity analysis will be conducted using per-protocol (PP) analysis, which consists of all participants who meet all eligibility criteria and are randomized, complete the treatment and follow-up plan, without any major protocol deviations.

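### Free improvement, not an error: the primary chi-squared test is valid but leaves baseline ISI, collected on everyone, unused as a covariate

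*Protocol article*

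**What the plan says.** Section 2.6.1 defines the primary outcome as the "proportion of participants whose average Insomnia Severity Index (ISI) scores decrease by at least 7 units" between baseline and Week 4. It gives the scale as "consisting of a total score ranging from 0 to 28" and the reason for the cut-off: "The minimal clinically important difference (MCID) of ISI is 7 units". Section 2.2.2 admits participants with a baseline ISI of 15 or more.

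For the analysis, section 2.8 states that "a Chi-squared test will be applied to compare the response rate between treatment group and control group", and that "α will be set at 0.025 for the primary outcome". It names no covariate for this comparison. Section 2.6.2 has ISI measured at baseline, Week 4 and Week 8, and section 2.8 analyses the continuous score as a secondary outcome in a repeated-measures mixed model, listed with seven other measures. Section 2.3 describes 1:1 allocation in blocks of 4 or 6 and mentions no stratification. On size, section 2.7 says that "recruitment will take place for a participant sample size of 60, with 30 individuals per group", and that "A formal sample size calculation is not necessary in our exploratory study".

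**The concern.** Blocks of 4 or 6 keep the arm sizes equal but do not balance ISI severity. With 30 per arm, the groups can differ at baseline by chance. If participants with higher entry scores tend to fall further, as regression to the mean would produce, such a difference adds noise to the unadjusted comparison of response rates. A covariate that is already recorded could remove that noise.

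The sample is fixed without a power calculation, alpha is set below 0.05, and the Discussion accepts that the small sample may miss a real effect. Making better use of the data is therefore the one gain available without more patients. What is at stake is precision. The error rate and the direction of the estimate are not in question.

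**Working it through.** **No figure to reproduce.** The plan states no power, effect or response rates for N = 60, so every outcome-model input below is an assumption.

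**From the protocol:** 30 per arm; ISI 0 to 28; entry at 15 or more; response = fall of at least 7; alpha 0.025 (sidedness not stated, taken as two-sided).

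**Assumed:** baseline ISI normal (19, 3.5) truncated to 15–28, realised SD about 2.87; mean sham fall of 4 points; true effect 4 points; residual SD 5; slope of Week 4 ISI on baseline varied from 0 to 1.

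**Step 1: can everyone respond?** The lowest entry score gives 15 − 7 = 8, above the floor of 0. Every eligible participant can fall 7 points.

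**Step 2: does baseline shift the chance of response?** In the sham arm the expected fall at baseline b is 4 + (1 − slope)(b − 19). Scores are whole numbers, so P(response) ≈ Φ{[4 + (1 − slope)(b − 19) − 6.5]/5}.

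- Slope 0.3: b = 15 gives Φ(−1.06) = 14%; b = 24 gives Φ(0.20) = 58%.
- Slope 1.0: Φ(−0.50) = 31% at every baseline.

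The dependence rests entirely on a slope that the documents do not give. In the simulations below, the correlation between baseline and response ran from 0.00 (slope 1) to 0.38 (slope 0). Baseline thus explained at most 0.38² = 14% of the variance in response.

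**Step 3: chance imbalance.** The SE of the difference in baseline means is 2.87 × √(2/30) = 0.74. The chance of a gap above 1 point is 2[1 − Φ(1/0.74)], about 18%; simulation gave 16–19%. At slope 0.3, one point of imbalance moves the sham response rate by about 0.7 × φ(0.5)/5 = 0.7 × 0.352/5 = 4.9 percentage points. Simulation gave 4.5–5 for the risk difference, and adjustment removed the shift. At slope 1.0 there is none.

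**Step 4: power, 1,500 simulated trials per row.** The analyses are:

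- Chi-squared: z = (p₁ − p₀)/√[2p̄(1 − p̄)/30].
- Adjusted logistic: logit P = β₀ + β₁·arm + β₂·baseline ISI, likelihood-ratio test of β₁.
- Adjusted score: Week 4 ISI regressed on arm and baseline ISI.

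| Slope | Response sham / EA | Chi-squared | Adjusted logistic | Adjusted Week 4 score | Gain from covariate | Remaining gap to score |
|---|---|---|---|---|---|---|
| 0.0 | 37% / 64% | 48.1% | 54.3% | 78.6% | +6.2 | 24.3 |
| 0.3 | 36% / 64% | 51.7% | 55.9% | 76.8% | +4.2 | 20.9 |
| 0.5 | 34% / 64% | 55.3% | 56.5% | 77.5% | +1.2 | 21.0 |
| 0.7 | 32% / 62% | 57.3% | 57.1% | 76.9% | −0.2 | 19.8 |
| 1.0 | 31% / 62% | 59.2% | 58.8% | 77.4% | −0.4 | 18.6 |

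The Monte Carlo SE of one power figure is about √(0.55 × 0.45/1500) = 1.3 points. The adjusted-to-unadjusted variance ratio of the risk difference (linear probability model), from slope 0 to 1, was 0.86, 0.93, 0.97, 1.00 and 1.02. That linear model gained 4.5 points at slope 0 and 3.3 at slope 0.3, and lost 0.2 to 1.4 points from slope 0.5 upward.

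At slope 0.5 with other inputs, the covariate gained 3.4 points (46.9% to 50.3%; effect 3, SD 4) and 1.2 points (60.1% to 61.3%; effect 5, SD 6).

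A separate simulation at the same alpha and effect gave chi-squared 50–63%, adjusted logistic 55–63% and adjusted score 76–80%. The total gap between chi-squared and score is then 80 − 63 = 17 to 76 − 50 = 26 points.

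**Step 5: error rate under no effect (slope 0.5).** Chi-squared 2.9%, adjusted logistic 3.3%, adjusted score 2.9%, against a nominal 2.5% (Monte Carlo SE 0.4 points). All are close to nominal. The logistic figure is the highest, so a small part of its apparent gain may be slight liberality.

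**The case against.** The strongest reply is that nothing here is wrong. The chi-squared test controls error, chance imbalance is already part of the sampling variation it allows for, and baseline enters the endpoint through the change score. The cut-off rests on a stated MCID. The trial is an openly exploratory pilot, and continuous ISI is already a prespecified secondary outcome under a mixed model. How that model handles baseline can properly be left to a SAP. The gain for the responder test is small, and nil when the slope is near 1. Enrolment was due to end in June 2024 and the article appeared in April 2025, so the window for changing a primary analysis may have closed.

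Most of this stands, and it limits the point to a suggestion. It does not remove it: section 2.8 does name the primary test, so that choice is open to comment, and the covariate costs nothing to use.

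A reader might infer that baseline largely determines who can drop 7 points. The documents do not support that: the entry rule leaves everyone room to fall 7 points, and no data link baseline to response. A reader might also infer that the unadjusted result is biased. It is not; imbalance by chance affects single trials in either direction and averages out.

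**Conclusion.** The planned primary test is sound but slightly inefficient. Adding baseline ISI gains about 0 to 6 power points, the upper end only when Week 4 ISI depends weakly on baseline, and protects the estimate against chance imbalance when the slope is below 1. It never costs power materially.

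The bigger loss is due mainly to dichotomising. Once baseline is adjusted for in both analyses, the responder test is still about 19 to 24 points below the Week 4 score in the table above. Adjusting the responder test does not recover that, so the large gap argues for giving the continuous result more weight; it does not measure the cost of omitting the covariate.

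All sizes depend on the assumed baseline distribution, residual SD, effect and slope, none of which the protocol supplies.

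**What to change.** In section 2.8, and in the SAP if there is one:

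- Keep the 7-point responder endpoint.
- Make its primary analysis a logistic regression on arm and baseline ISI, reported as a standardised (marginal) risk difference with a confidence interval. The adjusted odds ratio is conditional on baseline and is not comparable with the unadjusted one, which is why the marginal risk difference should lead.
- Retain the chi-squared test as a sensitivity analysis.
- Name the Week 4 ISI difference, adjusted for baseline, as the key supporting result, always reported beside the responder result.

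The cost is a few sentences and a few lines of code, with no new data. The change must be dated before unblinding. If the data have already been unblinded, keep the chi-squared test as primary and present the adjusted analyses as supportive, labelled as added later.

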### Randomization and allocation concealment

2.3.

Participants will be randomly allocated in a 1:1 ratio to either the treatment group (EA) or control group (sham EA). An independent statistician, who will not be involved in the later implementation or statistical analysis, will generate the randomization sequence using block randomization with a block size of 6 or 4 *via* R software (4.2.1). The enrollment number will be written on the cover of an opaque envelope where the randomization sequence will be placed. The Research Center of Clinical Epidemiology (Beijing Institute of Traditional Chinese Medicine) will provide a randomization sequence and opaque envelopes. Researchers will be required to open the envelope according to the enrollment order of participants and apply the treatment instructions specified for their respective groups [22].

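### The single primary chi-squared test is judged at α = 0.025, with no reason or sidedness given, while its effect is reported with a 95% CI, so the two can disagree on significance

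*Protocol article*

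**What the plan says.** Protocol article, section 2.8 (Statistical analysis), makes three statements about the primary outcome:

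- The test: "a Chi-squared test will be applied to compare the response rate between treatment group and control group".
- The threshold: "α will be set at 0.025 for the primary outcome, and it will be set at 0.05 for multiple comparisons of the secondary outcomes".
- The interval: "the 95% confidence interval (95% CI) will be used to assess effect size of primary and secondary outcomes".

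The rest of the article leaves only one primary test. Section 2.6.1 defines one endpoint, assessed at Week 4: "The primary is the response rate, which reflects the proportion of participants whose average Insomnia Severity Index (ISI) scores decrease by at least 7 units". The Discussion describes one comparison: "we will conduct a single-center and two-arm RCT". Section 2.7 sets the size: "recruitment will take place for a participant sample size of 60, with 30 individuals per group". It also says "A formal sample size calculation is not necessary in our exploratory study", so there is no power calculation that could explain 0.025. Section 2.1 mentions quarterly ethics audits that consider early termination, but no interim test of efficacy. No section says whether 0.025 is one-sided or two-sided.

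**The concern.** A threshold of 0.025 usually signals either a one-sided test or a two-sided 0.05 split over two tests. The article describes no second primary endpoint, third arm, second primary time point or interim look that would call for a split. It also names a chi-squared test, which has no direction. On the plain reading, the primary p-value faces a stricter error level than the interval printed beside it.

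What is at stake is the wording of the main result. For a band of plausible outcomes, the test would call the trial non-significant while the interval excludes no effect. If this is settled only after the data are seen, the choice of which to emphasise decides whether the primary result is called positive. The stricter level also costs power in a trial of 60, and the article gives no reason for paying that cost.

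**Working it through.** **Inputs.** From section 2.8: α = 0.025 for the primary outcome, a 95% CI and a chi-squared test. From section 2.7: 30 per arm. The article gives no response rates, so those below are assumptions. Dropout is taken as zero. There is no sample-size calculation to reproduce.

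**1. Critical values (chi-squared, 1 df).**
- p < 0.025 requires chi-squared ≥ 5.024, i.e. |z| ≥ 2.241, which matches a 97.5% interval.
- p < 0.05 requires chi-squared ≥ 3.841, i.e. |z| ≥ 1.960, which matches a 95% interval.

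Results between 3.841 and 5.024 are where the two stated rules part.

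**2. Worked example, 17/30 against 9/30.**
- Difference D = 0.5667 − 0.3000 = 0.2667; pooled rate 26/60 = 0.4333.
- Pearson chi-squared = D² / [0.4333 × 0.5667 × (2/30)] = 0.0711 / 0.01637 = 4.34, p = 0.037. This misses 0.025.
- Wilson 95% limits: 0.392 to 0.726 for 17/30, and 0.167 to 0.479 for 9/30.
- Newcombe lower limit = 0.2667 − √[(0.5667 − 0.392)² + (0.479 − 0.300)²] = +0.017.
- Newcombe upper limit = 0.2667 + √[(0.726 − 0.5667)² + (0.300 − 0.167)²] = +0.475.

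The 95% CI is +1.7 to +47.5 points and excludes zero. The same construction at 97.5% gives −1.8 to +49.8 points, which agrees with the test. A second example, 14/30 against 6/30, gives p = 0.028 and a Newcombe 95% CI of +2.8 to +46.8 points.

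**3. How often, and the power given up.** All 31 × 31 possible tables were enumerated with binomial weights, using the uncorrected Pearson test and the Newcombe 95% CI.

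| Assumed sham vs EA rate | Power at 0.05 | Power at 0.025 | Loss (points) | CI excludes 0 but p ≥ 0.025 |
|---|---|---|---|---|
| 25% vs 50% | 51.6% | 41.3% | 10.3 | 10.3% |
| 30% vs 60% | 66.3% | 56.1% | 10.2 | 10.2% |
| 20% vs 50% | 69.2% | 59.6% | 9.6 | 9.6% |

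The reverse conflict (p < 0.025 while the CI includes zero) has probability 0.000 in every scenario. With equal true rates of 20% to 40%, the one-way conflict has probability about 2%. With Wald intervals it is somewhat higher: about 13% at 20% vs 45%, 12% at 20% vs 50%, and about 3% under no difference.

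Over a wider assumed range (sham 10–40%, difference 20–40 points), the normal approximation puts the power loss at about 5 to 12 points.

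**4. Type I error.** With equal true rates of 20% or 30%, the test at 0.025 rejects in 2.6% of trials. If the 95% CI were read as the decision rule instead, the rate would be about 2.6% + 2% ≈ 5%, twice the declared level.

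**5. Continuity correction.** Section 2.8 does not say whether the chi-squared test is corrected. For 17/30 against 9/30 the corrected statistic is (0.2667 − 1/30)² / 0.01637 = 3.33, p = 0.068. A corrected test at 0.05 would therefore still disagree with the 95% CI, about 10% of the time at the same rates. Changing α alone does not finish the repair.

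**The case against.** The strongest reply is that one-sided 0.025 was meant. The Discussion states a directional hypothesis in favour of electroacupuncture, and one-sided 0.025 uses z = 1.960, the same as a two-sided 95% CI. On that reading test and interval agree, and no power is lost relative to two-sided 0.05. This is a fair possibility, but the article does not state it and the named test is not directional. An analyst who compares the printed chi-squared p-value with 0.025 would in effect be applying one-sided 0.0125. The intent has to be written down. A fuller plan may state the sidedness; the point here is not that omission but two stated levels that do not match as they stand.

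A second reply is that the interval is there only to describe effect size, so the test decides. That is also fair, and it limits the harm. The stated α then holds and the interval is simply narrower than the test implies. A third reply is that this is a self-described exploratory pilot whose Discussion already concedes limited power. That lowers the weight of the point but does not remove it.

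Several stronger readings are tempting and should not be drawn:

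- **That test and interval can point in opposite directions.** They cannot; the only conflict is an interval excluding zero with p between about 0.025 and 0.05.
- **That false positives are inflated.** They are not if the test governs; 0.025 is the conservative choice.
- **That it is an error for the primary threshold to be stricter than the secondary one.** It breaks no rule.
- **That each secondary outcome is tested at an uncontrolled 0.05.** The text sets 0.05 for multiple comparisons, which can mean a family-wise level, and many of the outcomes are correlated. The article does not support a figure for false-positive risk.

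**Conclusion.** The point holds, at moderate weight. Section 2.8 pairs a non-directional test at 0.025 with a 95% CI for one outcome, one time point and one comparison, and gives no reason or sidedness. As written, the two disagree whenever p falls between about 0.025 and 0.05. This happens in about 10% of trials at the three assumed pairs of rates and about 2% when there is no difference, always with the CI excluding zero and the test failing.

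The power cost of about 10 points rests on assumed response rates, full follow-up, and the two-sided reading of 0.025. If one-sided 0.025 was intended, the conflict and the loss both disappear once that is stated, since it equals two-sided 0.05 for the chi-squared p-value. The mismatch between the two levels as written does not depend on the assumed rates.

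**What to change.** Before unblinding, amend section 2.8 in one of two ways:

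1. **Preferred.** State a two-sided α of 0.05 for the single primary comparison, tested with the Pearson chi-squared test without continuity correction. Report the risk difference with a compatible 95% CI, such as Newcombe's. If one-sided 0.025 was meant, say so and note that it equals two-sided 0.05 for the chi-squared p-value.
2. **If two-sided 0.025 is deliberate.** Give the reason and report a 97.5% CI for the primary risk difference, again with the uncorrected test.

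In both cases, add that the test decides significance and the interval describes the effect, because the two methods are not algebraically identical. The interval method should be named. For 14/30 against 6/30 (p = 0.028), a Wald 97.5% interval runs from +0.5 to +52.8 points and excludes zero although the test misses 0.025.

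The cost is one or two sentences, with no extra patients, visits or data. Timing matters more than effort: the choice should be dated before the allocation is revealed, so that it cannot be guided by the result.
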